## Abstract

**Background:**

The stress of a breast cancer diagnosis and its treatment can produce a variety of psychosocial sequelae including impaired immune responses. Mindfulness Based Stress Reduction (MBSR) is a structured complementary program that incorporates meditation, yoga and mind-body exercises. Despite promising empirical evidence for the efficacy of MBSR, there is a need for randomized controlled trials (RCT). There is also a need for RCTs investigating the efficacy of psychosocial interventions on mood disorder and immune response in women with breast cancer. Therefore, the overall aim is to determine the efficacy of a Mindfulness Based Stress Reduction (MBSR) intervention on well-being and immune response in women with breast cancer.

**Methods and design:**

In this RCT, patients diagnosed with breast cancer, will consecutively be recruited to participate. Participants will be randomized into one of three groups: MBSR Intervention I (weekly group sessions + self-instructing program), MBSR Intervention II (self-instructing program), and Controls (non-MBSR). Data will be collected before start of intervention, and 3, 6, and 12 months and thereafter yearly up to 5 years. This study may contribute to evidence-based knowledge concerning the efficacy of MBSR to support patient empowerment to regain health in breast cancer disease.

**Discussion:**

The present study may contribute to evidence-based knowledge concerning the efficacy of mindfulness training to support patient empowerment to regain health in a breast cancer disease. If MBSR is effective for symptom relief and quality of life, the method will have significant clinical relevance that may generate standard of care for patients with breast cancer.

**Trial registration:**

ClinicalTrials.gov: NCT01591915

## Background

Breast cancer is one of the most feared diseases among women, and for many women a breast cancer diagnosis and its subsequent treatment are accompanied by dealing with a spectrum of physical and psychological challenges [1,2]. Women with breast cancer are at risk of psychological morbidity [3], and up to 30% of women diagnosed with breast cancer develop mood disorder, either anxiety or depressive symptoms, within one year of diagnosis [4,5]. While breast cancer is a major stressor for any woman, there is great variability in women’s emotional responses and their ability to mobilize the resources to cope with distress. However, although levels of distress tend to decrease over time, a subset of women with breast cancer remain highly distressed [6,7]. A growing area of interest is the personal growth and transformation of individuals as they adjust to a life-altering event and an increasing body of literature illustrates that many people experience significant personal growth despite severe trauma or disease [8,9]. Notwithstanding recurrent breast cancer, women who view their disease as a challenge and an opportunity for personal change are able to create wellness by being in the present moment [10].

The stress of a breast cancer diagnosis and its treatment can produce a variety of psychosocial sequelae including impaired immune responses [11]. An increasing body of research indicates that stress-related psychosocial factors are associated with higher cancer incidence and higher mortality [12]. Data suggest that psychological stress has a significant negative effect on cellular immune responses, such as lowered natural killer cells (NK cells) and T lymphocytes (T cells) [13]. Previous research indicates that NK and T cells are sensitive to different aspects of the stress response in women with breast cancer [14]. In addition, T cells have been linked to recurrence [15] and survival [16]. Other important parameters are cytokines, such as interleukin-6 (IL-6) and interleukin-8 (IL-8), which independently show correlations with breast cancer disease stage and progression [17-20].

The recognition of psychosocial needs in cancer patients has led to the development of psychosocial interventions, indicating a variety of positive effects on coping, quality of life, emotional and functional adjustment [21,22]. The literature on psychosocial interventions for cancer fails to meet criteria for establishing treatment efficacy and does not address issues of cost-effectiveness [23]. Although evidence suggests beneficial effects of psychosocial interventions [21,22], the physiological benefits for breast cancer patients remain unclear [24]. Furthermore, there are no existing large-scale studies prospectively investigating the efficacy of psychosocial intervention on coping and immune response in women with breast cancer [24].

Mindfulness Based Stress Reduction (MBSR) is a standardized program incorporating mindfulness meditation, yoga practices and other techniques designed to reduce suffering and improve health and well-being in patients with a wide range of chronic pain and stress disorders [25-27]. MBSR has also been shown to improve mood and reduce symptoms of stress in mixed groups of cancer patients [28]. The primary goal of MBSR is to develop the capacity to be aware in each moment, by “paying attention in a particular way: on purpose, in the present moment, and non-judgmentally” [25]. MBSR is a structured group-formatted 8-week course, attended once a week by patients for an average of 2 hours, together with daily practice of homework assignments. While noting the efficacy of MBSR on different patient populations, several reviews have pointed out the inherent methodological problems in the published studies [29,30]. Two systematic reviews of MBSR interventions for the treatment of anxiety and depression emphasize the methodological shortcomings which create uncertainties about the efficacy of treatment. The reviewed studies that reported a statistically significant reduction in anxiety and depression did not include control groups or follow-up data, and future studies with improved methodologies are needed to test the efficacy of the mindfulness component of the intervention [31,32].

The MBSR program was shown to have beneficial effects on immune function, reduced cortisol levels, improved Quality of Life (QoL), and increased coping effectiveness in a non-randomized group of women with breast cancer as compared with women who received the usual care [33]. A recent randomized study [34] showed that cancer patients who received a mindfulness intervention reported less perceived stress and posttraumatic avoidance symptoms and increased positive states of mind. This study indicates that the improvements in psychological well-being resulting from the MBSR intervention could have been explained in terms of increased levels of mindfulness. Other study results indicate a positive adjustment of cortisol levels as a result on MBSR program [35]. Evidence from uncontrolled studies of breast and prostate cancer patients also suggests that MBSR improved QoL and decreased stress symptoms [36], and altered cortisol and immune patterns [37]. Study results suggest that MBSR may influence the functioning of the hypothalamic-pituitary-adrenocortical (HPA) axis [35,38]. These pilot data from studies investigating the relationships between MBSR and hormone levels highlight the need for better-controlled studies in this area [38]. These results raise important questions as to whether mindfulness based interventions actually enhance mindfulness and whether such changes in mindfulness are related to positive outcome in the experience of health, strengthened immune system or disease-free survival.

Despite promising empirical evidence that the efficacy of MBSR improves mood and reduces symptoms of stress, there is a need for randomized, controlled studies including homogenous patient populations and using reproducible and stringent methodological procedures. In addition to self-reported psychosocial and functional measures of health and illness, assessment of biological markers are also needed in future mindfulness based interventions [30].

### Aim and outcome measurements

The overall aim is to determine the efficacy of a Mindfulness Based Stress Reduction (MBSR) intervention on well-being and immune response in women with breast cancer. This paper presents in-depth information on the design of the study (Figure 1). The study design follows the Consort recommendations [39-41].

**Figure 1 F1:**
[figure not shown]
**Study design including enrollment, allocation and follow-up.** MBSR = Mindfulness Based Stress Reduction.

#### Primary outcome

The efficacy of MBSR on mood disorders, evaluated in terms of anxiety and depression.

#### Secondary outcomes

The efficacy of MBSR on:

● coping capacity,

● symptom experience,

● quality of life,

● health status,

● personal growth,

● level of mindfulness,

● physiological response, disease progression, survival,

● analyses of utility and health economics, and

● analyses of the usability of MBSR in clinical care.

## Methods

### Design

Patients diagnosed with early stage breast cancer will be consecutively recruited from two surgical centers, to participate in this three-armed randomized controlled complementary intervention study. The study design is presented in Figure 1.

Written consent will be obtained before enrolment. Confidentiality will be assured, and participants will be advised that they are free to withdraw from the study at any time, and respect will be given to the participant’s condition. The study is registered in ClinicalTrials.gov: NCT01591915.

### Participants

In this randomized, controlled intervention study, patients diagnosed with breast cancer will be consecutively recruited to participate after completion of adjuvant chemotherapy, with/or without endocrine therapy.

Research nurses will contact eligible patients at the first follow-up appointment for patients receiving hormonal therapy or at the last treatment for patients undergoing chemotherapy. After oral and written information, interested patients will provide written consent to participate in the study. Participants who agree to participate will be invited to a first baseline health check-up appointment, including collection of blood samples, completion of questionnaires, a health check-up, and finally random assignment to one of three groups. Randomization will be conducted in blocks of 9, 12 and 15 blocks varied randomly. The assignment codes will be kept in sequentially numbered, opaque, sealed envelopes, prepared by the research team. At the time of allocation, the research nurse will pick the sequential envelope, write the participant’s name and personal registration number on the envelope, and then open it.

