#### Inclusion criteria

Patients diagnosed with early-stage breast cancer:

receiving hormonal therapy, or:

after completion of adjuvant chemotherapy,

with or without radiotherapy

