### Data collection

Socio-demographic data will be collected through chart review and interviews. Data characteristics are age, marital status, living situation, employment status, children, occupation and educational level. Clinical characteristics investigated are type of treatment, tumor characteristics, and co-morbidity. Patient self-reported response (questionnaires) and immune response (blood samples) will be collected, and health checks conducted, at baseline (before start of intervention), after the intervention for MBSR Intervention groups I and II, follow-up will be conducted one months after the intervention, and at similar time points of 3 months (non-MBSR), 6 months, 12 months, and thereafter yearly up to 5 years. Health checks including current health status and treatment, and blood samples will be performed by research nurses. Patient outcome will be collected by following the questionnaires, health check-ups and bio-markers.

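### The article contradicts itself on whether women on endocrine therapy alone are eligible; the text must be reconciled and, if both routes enter, treatment route named as a covariate

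*Protocol article*

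**What the plan says.** Three statements in the protocol article bear on who may enter.

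- Participants, opening sentence: women are "consecutively recruited to participate after completion of adjuvant chemotherapy, with/or without endocrine therapy".
- Inclusion criteria: early-stage breast cancer and "receiving hormonal therapy, or" else "after completion of adjuvant chemotherapy", with or without radiotherapy.
- Participants, second paragraph: research nurses make contact "at the first follow-up appointment for patients receiving hormonal therapy or at the last treatment for patients undergoing chemotherapy".

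On allocation, the article says "Randomization will be conducted in blocks of 9, 12 and 15 blocks varied randomly" and "The assignment codes will be kept in sequentially numbered, opaque, sealed envelopes". Women are "consecutively recruited from two surgical centers". No stratification factor is named. Data collection states: "Clinical characteristics investigated are type of treatment, tumor characteristics, and co-morbidity". Statistical analyses gives repeated-measures ANOVA/MANOVA for the comparison between groups and names no covariate for it. The sample size section sets 50 women per group and a target difference of 1 HAD unit in change from baseline to 3 months.

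**The concern.** The opening sentence of Participants makes completed chemotherapy universal and endocrine therapy optional. The Inclusion criteria make the two treatments alternatives. A woman treated with endocrine therapy and no chemotherapy fails the first statement and passes the second. Because recruitment is consecutive, the choice between them settles which women are approached, and later which women the results describe.

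A secondary matter follows if both routes are enrolled. Route then fixes when a woman enters relative to her treatment: at her last chemotherapy treatment, or at a first follow-up on hormonal therapy. The power calculation rests on change over 3 months, and the Background says that distress tends to fall with time. Women who start at different points of recovery could therefore change by different amounts whatever arm they are in. That would add variance to the contrast, and a chance difference between arms in the mix of routes would move the estimate.

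**Working it through.** **Eligibility.** The three statements, applied to a woman on endocrine therapy who has had no chemotherapy:

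| Place | Eligible? |
|---|---|
| Participants, opening sentence | No: chemotherapy must be complete |
| Inclusion criteria | Yes: hormonal therapy is sufficient |
| Participants, contact instruction | Most naturally yes: she has her own contact point |

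The first and second rows cannot both hold. The third leans towards the second but does not settle the matter, since a woman who had chemotherapy and then endocrine therapy also fits its wording.

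**Size of chance imbalance, if both routes enter.**

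Inputs: 50 per arm (Sample size calculation). Chemotherapy share p is not given; 30-70% is assumed.

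SD of the difference in share between two arms = √(2p(1−p)/50).

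- p = 0.5: √(2 × 0.25/50) = 0.100.
- p = 0.3 or 0.7: √(2 × 0.21/50) = 0.092.

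Probability that two given arms differ by 20 points or more:

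| Share | Independent binomial arms | Simulated blocks of 9, 12, 15 |
|---|---|---|
| 50% | 5.7% | 4.8% |
| 30% or 70% | 3.8% | 3.1-3.4% |

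In the block simulation (10,000 allocations of 150 women, no stratification), the largest and smallest of the three arms differ by 20 points or more in about 12% of trials at a 50% share, and in about 8% at 30% or 70%.

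**Effect on the HAD contrast.** Shift = imbalance × route difference in 3-month change. The route difference is not given; 0.5-2 HAD units is assumed.

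- 10-point imbalance: 0.10 × 0.5 = 0.05 to 0.10 × 2 = 0.2 unit.
- 20-point imbalance: 0.20 × 0.5 = 0.1 to 0.20 × 2 = 0.4 unit.

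The target is 1 unit.

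**What adjustment gains.** The article states no SD, so its 50 per group can be neither reproduced nor refuted. Solving backwards for a pairwise two-sided test at 0.05 with 80% power gives SD = √(50/(2 × (1.960 + 0.842)²)) ≈ 1.79. The unadjusted standard error is then 1.79 × √(2/50) = 0.358. Removing the route component leaves a standard error of √(1.79² − p(1−p)δ²) × 0.2, where δ is the route difference. At p = 0.5:

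- δ = 0.5: √(3.204 − 0.0625) × 0.2 = 0.354.
- δ = 1: √(3.204 − 0.25) × 0.2 = 0.344.
- δ = 2: √(3.204 − 1) × 0.2 = 0.297.

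With an assumed SD of 3, the standard error falls from 0.600 to 0.598 at δ = 0.5 and to 0.592 at δ = 1, under 2% in both cases; at δ = 2 it falls to 0.566. The gain is small unless the route difference is large.

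**The case against.** On eligibility, it can be said that the Inclusion criteria are the labelled list, that the contact instruction agrees with them, and that the opening sentence of Participants is only loosely worded. That tempers any claim that nurses would in practice enrol different populations. It does not remove the contradiction: both statements are positive, they are incompatible, and nothing says which governs. This is not a detail lost through condensing a longer document.

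On randomisation, a reader might infer that the trial leaves a strong prognostic factor unbalanced and must therefore stratify by route and centre. The article does not support that, for four reasons.

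- Nothing in it shows that route predicts HAD change or immune response. The Background links stress with distress and with NK and T cells, but never compares women after chemotherapy with women on endocrine therapy alone.
- Randomisation balances route in expectation. Only chance imbalance remains, and the standard error of an unadjusted test already counts it; there is no bias and no inflation of type I error.
- An article may leave stratification factors to the full protocol, so silence is not evidence that there are none, nor that there is a single envelope series.
- The 0.4-unit shift needs both an uncommon imbalance and a route difference of twice the target effect.

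All four stand. For centre, the article offers no argument beyond there being two of them.

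**Conclusion.** The eligibility contradiction is established from the text alone and needs no assumption. It should be corrected because it defines the trial population. The documents do not settle which statement is intended.

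The statistical consequence is secondary and conditional on both routes being enrolled. It concerns precision and the chance error of a single trial, not validity. Its size rests on two assumptions, a chemotherapy share of 30-70% and a route difference of 0.5-2 HAD units; at the lower end of the latter it is negligible. Naming route as a covariate is worthwhile because it costs almost nothing. The absence of a named stratification factor is not in itself a fault.

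**What to change.** 1. Reconcile the opening sentence of Participants, the contact instruction and the Inclusion criteria to one statement of who is eligible, saying explicitly whether women on endocrine therapy without chemotherapy may enter. Cost: one sentence.
2. If both routes are enrolled, prespecify treatment route as a covariate in the between-arm models for HAD and the immune markers. Define it so that a woman who had both treatments falls in one stated category. In a repeated-measures model, let route act on change over time (route by time), since a main effect alone adjusts only the overall level. Cost: one model term, with its time interaction where the model is longitudinal. Type of treatment is already collected, so no new data are needed, and the step remains open if randomisation has begun.
3. Stratifying the envelopes by route is optional. It would bring the imbalance close to zero but requires separate envelope series, and the covariate secures most of the benefit.

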#### Inclusion criteria

Patients diagnosed with early-stage breast cancer:

receiving hormonal therapy, or:

after completion of adjuvant chemotherapy,

with or without radiotherapy

#### Exclusion criteria

Patients with other advanced illness at diagnosis, and/or:

ongoing major depression

ongoing Herceptin therapy

previously use of MBSR

### Training of instructors

Trained by a senior MBSR instructor, four registered nurses, skilled in patient learning, have been trained as certified MBSR instructors. Briefly, the instructor training consists of: 1 day of introduction to MBSR; 8 weeks of instructors’ own MBSR practice including 20 minutes sessions, 6 days/week; 2 days focused on practical training in group sessions; 8 week course in leading a group of patients who attend once a week for an average of 2 hours; 2 days focused on instructors’ experience of leading patient groups; and 1 day examination and certification.

### Intervention

It is well known that attention, expectations and good caring treatment contribute to the placebo effect. In order to minimize the impact of a situation with “a self-selected treatment and caring response to an enthusiastic therapist may be part of the active components of the alternative medical field” [42], two intervention groups and one control group will be included. All women receive standard care (SC) according to the national and local guidelines recommendations [43].

Participants will be randomized into one of three groups:

– SC and MBSR Intervention group I (8 weeks self-instructing program + instructor and weekly group sessions)

– SC and MBSR Intervention group II (8 weeks self-instructing program)

– SC and Non-MBSR (Controls)

Participants in MBSR Intervention group I and MBSR Intervention group II will participate in an 8-week tutorial of MBSR practice with homework assignments consisting of 20 minutes sessions, 6 days/week. Participants will be provided with information material including a 20-page introduction to mindfulness training, CD, diary and training program. Only participants in MBSR Intervention group I will take part in a structured group-formatted 8-week course that patients attend once a week for an average of 2 hours. Led by a certified MBSR instructor, these weekly group sessions will be focused on the participant’s experience of mindfulness, and include gentle yoga and meditation training. Owing to the differences between the two interventions groups, blinding will not be possible.

### Data collection

Socio-demographic data will be collected through chart review and interviews. Data characteristics are age, marital status, living situation, employment status, children, occupation and educational level. Clinical characteristics investigated are type of treatment, tumor characteristics, and co-morbidity. Patient self-reported response (questionnaires) and immune response (blood samples) will be collected, and health checks conducted, at baseline (before start of intervention), after the intervention for MBSR Intervention groups I and II, follow-up will be conducted one months after the intervention, and at similar time points of 3 months (non-MBSR), 6 months, 12 months, and thereafter yearly up to 5 years. Health checks including current health status and treatment, and blood samples will be performed by research nurses. Patient outcome will be collected by following the questionnaires, health check-ups and bio-markers.

### Measuring outcomes

#### Primary outcome

##### Mood disorder

The Hospital Anxiety and Depression Scale (HAD) is one of most widely used instruments to screen for anxiety and depression or psychosocial distress in cancer patients [44-46]. HAD is a 14-item questionnaire consisting of two sub-scales, anxiety and depression. Each response is rated on a four-point scale. Subscale scores range from 0 to 21. Scores of 0–7 indicate “normal”, 8–10 “borderline” and scores of >11 or more on either sub-scale are considered to represent risk of psychological morbidity [44-47]. The internal consistency of reliability for HAD Depression and HAD Anxiety are satisfactory, with Cronbach’s alpha 0.72 - 0.89, respectively 0.78 - 0.93 [46].

